#### *Selection bias*

We chose to collect surgery data from the Central Bureau of Statistics of the Netherlands to avoid selection bias induced by the fact that not all participants completed the questionnaire on putative risk factors (such as surgery) for a recurrent event. 95% of all patients are linked to CBS data, individuals who are not linked will be excluded from the analysis, an event that is considered to be random.

### **3. Statistical analysis**

#### **a. Methods**

Follow-up time will be calculated from the start of follow-up (i.e. 1. from stop date anticoagulant treatment after first VT and 2. from date of first VT onwards as a sensitivity analysis) until the end of follow-up (end of study, dead, recurrent event or loss to follow-up, whichever occurs first). The time window of surgery exposure for each individual is defined as 3-months from the surgery date. The total follow-up time in which patients are not exposed will be calculated as the total follow-up time minus the exposure time. As a sensitivity analysis, we will vary the time window of exposure because it is not known for how long the VT risk is increased after surgery. Therefore we will also consider a 1-month, 6-month and 1-year time window after surgery. We will calculate cumulative incidences for recurrent venous thrombosis for the exposed time windows and incidence rates by dividing the number of events by person-time for the exposed and the unexposed time periods.

Cox-proportional hazards modeling (with a time-dependent co-variate [surgery]) will be used to calculate a hazard ratio for developing recurrence. Also, we will estimate Hazard Ratios for several types of surgery on recurrence risk, and adjust for important confounders. Absolute risks for

recurrent VT will be calculated for several types of surgery (for all different time windows after exposure).

To identify high risk groups, we will perform a matched case-control study within this cohort. Cases are patients with a recurrent event who underwent surgery, controls are patients without a recurrent event who also underwent surgery. Cases and controls will be matched for [type of] surgery exposure. Four possible risk factors will be tested: 1. The presence of Factor V Leiden or non-O blood type or prothrombin mutation, 2. provoked or unprovoked first event, 3. DVT or PE as a first event and 4. sex. Odds ratios with 95% CIs will be calculated for these risk factors using logistic regression analysis. A prediction model will be developed if the number of cases is sufficient enough.

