| Neurosurgical                           |                    |                         |                                        |                          |                                       |
| Abdominal                               |                    |                         |                                        |                          |                                       |
| Minor abdominal                         |                    |                         |                                        |                          |                                       |
| Major abdominal                         |                    |                         |                                        |                          |                                       |
| Vascular                                |                    |                         |                                        |                          |                                       |
| Minor vascular                          |                    |                         |                                        |                          |                                       |
| Major vascular                          |                    |                         |                                        |                          |                                       |
| Non-orthopaedic day-care surgery |                    |                         |                                        |                          |                                       |
| VT recurrence risk                      | number of patients | 1-month
HR (95%CI)   | 3-month
HR adj * (95%CI) | 6-months
HR (95%CI)   | 1-year
HR adj * (95%CI) |
| No surgery                       |                    | ref                     | ref                                    | ref                      | ref                                   |
| Surgery (all)                    |                    |                         |                                        |                          |                                       |
| Orthopaedic surgery (all)        |                    |                         |                                        |                          |                                       |

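### The 1-, 3-, 6- and 12-month exposure windows all start at surgery, so the longer-window hazard ratios carry any early excess and do not by themselves show how long the risk lasts

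*Protocol*

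**What the plan says.** Protocol section 3a (Methods) fixes the main exposure: "The time window of surgery exposure for each individual is defined as 3-months from the surgery date". It then announces a sensitivity analysis and gives the reason: "we will vary the time window of exposure because it is not known for how long the VT risk is increased after surgery". The alternatives follow: "Therefore we will also consider a 1-month, 6-month and 1-year time window after surgery".

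Reference time is whatever lies outside the chosen window: "The total follow-up time in which patients are not exposed will be calculated as the total follow-up time minus the exposure time". The model is a Cox model with surgery as a time-dependent covariate ("Cox-proportional hazards modeling (with a time-dependent co-variate [surgery]) will be used to calculate a hazard ratio for developing recurrence"). Absolute measures are also planned: "We will calculate cumulative incidences for recurrent venous thrombosis for the exposed time windows and incidence rates", the rates being for exposed and unexposed time.

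The HR table in section 4b has one column per window, each against no surgery. The 1- and 6-month columns are headed HR; the 3-month and 1-year columns are headed adjusted HR. The cumulative incidence table uses the same four times. No HR for a separate later interval, such as months 4 to 6, is planned.

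**The concern.** The stated reason for varying the window is uncertainty about duration: "it is not known for how long the VT risk is increased after surgery". Windows that all open on the day of surgery answer a different question, namely the average relative hazard from surgery up to time w. If the excess is concentrated early, every longer window inherits it in diluted form. A 6- or 12-month HR above 1 is then compatible with no excess at all in the later months.

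This matters because the protocol's background section says that the results should guide physicians on prescribing anticoagulants, and notes that prevention comes at the cost of bleeding. How long the risk stays raised is something that readers will look for in the HR table, and the 1-year column invites the answer that it lasts a year.

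**Working it through.** The protocol gives no figure for duration. Its one design figure, the detectable relative risk in section 3b, has no bearing here. The check is whether the planned HRs separate different durations.

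**1. Window HR as an average.** Assumptions: constant background hazard, rare events, and little excess left in the reference. The HR for a window of w months from surgery is then about the mean of the monthly HRs:

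HR(w) = (h1 + h2 + ... + hw) / w.

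If the excess is k in month 1 and 1.0 afterwards, HR(w) = (k + w − 1)/w. At one year this is 1 + (k − 1)/12, above 1 for every k > 1.

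**2. Numbers (the true patterns are assumed).**

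| True pattern | 1 month | 3 months | 6 months | 12 months |
|---|---|---|---|---|
| HR 5 in month 1, then 1.0 | 5.00 | 7/3 = 2.33 | 10/6 = 1.67 | 16/12 = 1.33 |
| HR 10 in month 1, then 1.0 | 10 | 12/3 = 4.0 | 15/6 = 2.5 | 21/12 = 1.75 |
| HR 4 for 3 months, then 1.0 | 4 | 12/3 = 4.0 | 15/6 = 2.5 | 21/12 = 1.75 |

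The last two rows agree in the 3-, 6- and 12-month columns although the durations are one and three months. Only the 1-month column tells them apart.

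**3. Could the 1-year HR look convincing with no late excess?** Assume 473 operations (10% of 4731, the share assumed in section 3b), a background of 3% per year, and about 650 events in reference time. With HR 10 in month 1 only, the expected events within a year are 473 × 0.03/12 × 21 = 24.8. The 95% interval is 1.75 × exp(±1.96 × √(1/24.8 + 1/650)), or about 1.17 to 2.61. With HR 5 in month 1 only, the events are 473 × 0.03/12 × 16 = 18.9 and the interval around 1.33 is about 0.84 to 2.11. So it can, depending on the size of the early excess and the number of operations, which the protocol does not know.

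**4. What can be recovered.** Under the same assumptions the interval values follow by differencing. For months 2 and 3 the HR is (3 × HR(3) − HR(1))/2:
- HR 10 in month 1 only: (12 − 10)/2 = 1.0.
- HR 4 for three months: (12 − 4)/2 = 4.0.

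The four columns together therefore hold the information as point estimates. A confidence interval for the difference needs the covariance of overlapping estimates, which the table does not supply. As the table is headed, the formula would also subtract an unadjusted 1-month HR from an adjusted 3-month HR.

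**5. Changing reference.** In the 1-month analysis, months 2 to 12 after surgery count as unexposed. Assume monthly HRs of 6 (month 1), 3 (months 2-3), 1.5 (months 4-6) and 1 (months 7-12), with 10% operated once. The later excess is 2 × 2 + 3 × 0.5 = 5.5 months of background hazard. Over 5 years the reference is inflated by 0.1 × 5.5/(60 − 0.1) = 0.9%; with 3 or 7 years it is 1.5% or 0.7%. This is small.

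**6. Precision of disjoint intervals.** Background: 700/(4731 × 5) = 2.96% per year, with 5 years of follow-up assumed. For 473 operations this is 473 × 0.0296/12 = 1.17 events per month at HR 1. Under the pattern in step 5 the four intervals have 7.0, 7.0, 5.25 and 7.0 events. The factor exp(1.96/√events) is 2.1 for 7.0 events and 2.35 for 5.25. If the excess ends after month 1, months 2-3 hold only 2 × 1.17 = 2.3 events and months 4-6 hold 3.5, with factors of about 3.6 and 2.9.

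**The case against.** The best defence is that duration is not an objective. Section 1b lists absolute risk after surgery and risk factors, and section 3a calls the extra windows a sensitivity analysis. Read as a check on whether the main result depends on an uncertain exposure definition, varying the window from day 0 is legitimate. That stands, and it is why the window analysis should stay. It does not remove the problem that the reason given for varying the window is unknown duration.

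A reader might infer that duration cannot be recovered at all. The documents do not support this. The table has four columns, the two example rows differ in the first, and differencing gives rough interval values. Increments in the planned cumulative incidences, set against the unexposed rate, give a similar rough picture. A row falling from 10 to 1.75 also signals attenuation to a careful reader. But none of this is planned as an analysis, the cumulative incidences are not adjusted, and no confidence interval results.

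A reader might also infer that the changing reference seriously biases the HRs. At about 1% it does not.

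Finally, the coding of a time-dependent covariate could be left to an analysis plan that is not shown. The protocol nevertheless states the purpose, the windows, the reference and the table columns, and those already fix the contrast.

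**Conclusion.** The point holds in limited form. The 6- and 12-month HRs are averages from the day of surgery. An excess of HR k confined to month 1 still gives a 1-year HR of 1 + (k − 1)/12, for example 1.75 for k = 10, so neither HR can be cited alone as evidence that risk persists that long. What the plan lacks is an adjusted estimate, with a confidence interval, for each period after surgery.

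This rests on a roughly constant background hazard; the patterns and the numbers of operations are assumptions, because the protocol has no data on exposure frequency. It does not follow that the 3-month main estimate, the cumulative incidences or the stated objectives are wrong, and nothing in the protocol suggests that they are.

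**What to change.** Keep the 3-month main window, the 1-, 6- and 12-month sensitivity windows, and the cumulative incidences. Add one adjusted Cox model with disjoint time-dependent indicators for 0-1, >1-3, >3-6 and >6-12 months since the most recent operation. Use a single reference: time not within 12 months after any operation. Report it for all surgery and, where events allow, for all orthopaedic and all non-orthopaedic surgery. State that any conclusion about duration rests on this model and not on the 6- or 12-month window HRs. In the existing HR table, make clear for every column whether the HR is adjusted.

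The work is one recoded covariate and one extra table, from data already linked. The price is precision: for all surgery, about a factor of 2.1 to 2.35 either side of the HR with 5 to 7 events per interval (10% operated once, about 3% per year background), and more where an interval holds fewer events. A true HR of 1.0 in months 7 to 12 would have an interval of about 0.5 to 2.1. If events split evenly between orthopaedic and non-orthopaedic surgery (about 2.6 to 3.5 per interval), the factor is roughly 2.9 to 3.3. The model may therefore not locate the return to background precisely, and the report should say so.

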## **2. Study design**

### **a. Population description (inclusion/exclusion criteria)**

For this study we will use data from the MEGA follow-up study. 4731 patients with a first venous thrombosis were followed over time for recurrent venous thrombosis until 2008-2009. Information on the occurrence of a recurrent event was collected by means of a short questionnaire or patients were contacted by phone. Detailed information about the recurrent event was retrieved from questionnaires, anticoagulation clinics, treating physicians or cause of death statistics. At the end of study about 700 cases with a recurrent venous thrombosis were identified.

Participants completed a questionnaire on putative risk factors for recurrent venous thrombosis (including [type of] surgery). Despite this information, we will not use this data as information bias (recall bias) is likely to be present. The MEGA follow-up database has been linked to the Central Bureau of Statistics (CBS) database of the Netherlands with information on all surgical procedures (including dates) for all individuals that participated in the study. We will use these data to identify patients who underwent a surgical procedure during the period of interest.

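### The search for high-risk groups splits operated patients by recurrence yes or no, with no post-surgery window or time at risk, although the dated cohort allows a Cox analysis from the operation

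*Protocol*

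**What the plan says.** Objective 2 is to find risk factors for recurrence among patients with earlier venous thrombosis who are operated on. Section 3a (Methods) answers it with a design of its own: "To identify high risk groups, we will perform a matched case-control study within this cohort". The two groups are defined as follows: "Cases are patients with a recurrent event who underwent surgery, controls are patients without a recurrent event who also underwent surgery". On matching: "Cases and controls will be matched for [type of] surgery exposure". On analysis: "Odds ratios with 95% CIs will be calculated for these risk factors using logistic regression analysis". Four factors are tested: a combined genetic and blood-group factor, provoked or unprovoked first event, deep vein thrombosis or pulmonary embolism as first event, and sex. The paragraph ends: "A prediction model will be developed if the number of cases is sufficient enough".

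The case-control paragraph gives no post-surgery window, no matching on time, no control-to-case ratio and no reason for leaving the cohort design.

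The same document shows what is available. Section 2a describes a linked database "with information on all surgical procedures (including dates) for all individuals that participated in the study", and the paragraph on selection bias says that "95% of all patients are linked to CBS data". Earlier in section 3a, person-time, cumulative incidence and a time-to-event model are already planned on these patients: "Cox-proportional hazards modeling (with a time-dependent co-variate [surgery]) will be used to calculate a hazard ratio for developing recurrence". There, surgery exposure lasts 3 months from the operation, with 1 month, 6 months and 1 year as sensitivity windows.

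**The concern.** The cohort part of section 3a ties recurrence to a limited period after surgery and counts time at risk. The case-control part does neither. Read literally, a recurrence several years after an operation makes the patient a case, although the cohort analysis would place that event in unexposed time. A patient operated shortly before the end of follow-up is a full control, although that patient was hardly observed.

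Two things are at stake. The odds ratios may mainly describe long-term recurrence in people who were once operated on, which is a different question from who is at high risk because of surgery. And a factor that goes with longer or shorter follow-up after surgery would appear as a risk factor or a protective factor without being one.

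The output is also limited. The Background section wants individual risk estimates to guide prescribing, but absolute risks are planned by type of surgery and window, not by the four risk factors.

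**Working it through.** **The plan's own figure.** Section 3b states a detectable relative risk of 1.6 at 80% power for the main cohort comparison. There is no figure for the case-control part. With 4731 patients, 10% exposed (473 against 4258), 8% against 5%, and two-sided alpha 0.05 (assumed), the null-variance formula gives:

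- pooled risk = 0.1 × 0.08 + 0.9 × 0.05 = 0.053
- standard error = √[0.053 × 0.947 × (1/473 + 1/4258)] = 0.01086
- z = 0.03/0.01086 − 1.96 = 0.80, so power is 78.9% and the detectable relative risk is 1.61.

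The figure reproduces by this formula (the two-sided Fleiss formula gives 75.0%). It does not bear on the present point.

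**Step 1: how much of the case group is post-surgical.** Assume a constant background rate, raised by a factor k for the 3 months after surgery, and T years of follow-up after surgery. Ignoring depletion, the share of recurrences inside the window is 0.25k / (0.25k + T − 0.25). I take k = 1.6 from section 3b, and 3 and 10 from the range that the Background section cites; T = 2 and 4 years are assumptions.

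| k | T = 2 years | T = 4 years |
|---|---|---|
| 1.6 | 0.40/2.15 = 19% | 0.40/4.15 = 10% |
| 3 | 0.75/2.50 = 30% | 0.75/4.50 = 17% |
| 10 | 2.50/4.25 = 59% | 2.50/6.25 = 40% |

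Without a window, most cases fall outside the 3 months in all but one of these settings.

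**Step 2: unequal time at risk.** Take a factor with a true hazard ratio of 1, a constant hazard λ (2-5% per year, assumed), and follow-up after surgery of t1 years with the factor and t2 without. Risk is 1 − exp(−λt). At λ = 0.02, t1 = 2 and t2 = 4, the risks are 0.0392 and 0.0769, and the odds ratio is (0.0392/0.9608)/(0.0769/0.9231) = 0.49. Over λ = 2-5% it is 0.48-0.49; for 3 against 4 years it is 0.73-0.74. If follow-up does not differ by the factor, this bias does not arise.

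**Step 3: precision if controls are sampled.** Assume 473 operated patients (10% of 4731, before exclusions) and a recurrence risk of 5%, 8% or 14.8% (700/4731). With R non-cases per case and m controls per case, efficiency against keeping every operated non-case is (1 + 1/R)/(1 + 1/m). The interval on the log scale widens by 1/√efficiency.

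| Risk | Cases | R | 1:1 | 1:2 | 1:4 |
|---|---|---|---|---|---|
| 5% | 24 | 19.0 | 53% (38% wider) | 70% (19%) | 84% (9%) |
| 8% | 38 | 11.5 | 54% (36%) | 72% (17%) | 87% (7%) |
| 14.8% | 70 | 5.76 | 59% (31%) | 78% (13%) | 94% (3%) |

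The loss is 41-47% at 1:1, 22-30% at 1:2 and 6-16% at 1:4. It is nil when m = R.

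For a factor present in half the patients, the detectable odds ratio at 80% power is exp{2.80 × √[(1/cases + 1/controls)/0.25]}. With 38 cases this is 2.58 using all non-cases, 2.77 at 1:4, 3.05 at 1:2 and 3.63 at 1:1.

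**The case against.** A nested case-control analysis is a valid way to estimate relative effects, and Objective 2 asks only for risk factors. Four objections deserve weight.

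- **The window may be meant to carry over.** The matching sentence speaks of surgery exposure, which section 3a defines as 3 months. If so, only operations in the last 3 months of follow-up are truncated and the bias in Step 2 becomes small. But the definition of cases asks only that the patient was operated on and recurred. The two parts have to be tied together in the text.
- **Bias needs a link between factor and follow-up.** This stands. The protocol gives no sign that sex, genotype or type of first event goes with length of follow-up, so 0.49 is an illustration and not a forecast. Step 1 needs no such link.
- **A reader might infer that patients are necessarily discarded.** The protocol does not support this. It states no ratio, and matching by strata could keep every operated non-case, at no loss.
- **A reader might infer that the design cannot give absolute risks, or that every factor is on file for everyone.** Neither is supported. In an enumerated cohort, known sampling fractions would allow absolute risks, and absolute risks by type of surgery are planned from the full cohort. What is not planned is absolute risk by risk-factor group. Surgery dates and outcome are documented for the linked cohort, but nothing says that Factor V Leiden, prothrombin mutation and blood group are known for every operated patient.

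**Conclusion.** The point holds as a weakness of the analysis as written. Cases and controls are defined by recurrence alone, without a window or time at risk, while dated surgery, recurrence and follow-up exist for the linked cohort and a Cox model on it is already planned. The odds ratios therefore need not describe post-surgical recurrence: under the assumptions of Step 1, between 10% and 59% of cases would fall inside 3 months. They are biased for any factor related to length of follow-up, by an amount that the documents do not allow one to predict.

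The precision loss is conditional on the unstated control ratio, and rests on assumed counts, since section 3b says the frequency of surgery is unknown. The gap in absolute risk is one of planning, not of feasibility. The change should be made before the analysis; the main cohort comparison is not affected.

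**What to change.** Replace the case-control paragraph in section 3a with a cohort analysis:

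- include all operated, linked, cancer-free patients;
- fit a Cox model with time from the operation date to recurrence, censoring or the end of the 3-month window, with the other planned windows as sensitivity analyses;
- stratify by type of surgery, and enter the four risk factors and age;
- report hazard ratios and cumulative incidence per risk group;
- base any prediction model on these data, so that a baseline risk is available.

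The cost is a change of wording, with no new surgery or outcome data. Three limits should be stated. Repeat operations in one patient need a robust variance or a first-operation rule. The genetic and blood-group factor can be analysed only where it is known, or with imputation, because its completeness is not stated. A 3-month window will also leave fewer events than a definition without a window, so the number of events per window should be reported with the estimates.

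If the sponsor prefers to keep a case-control design, the text should at least apply the 3-month window to cases, choose controls from patients still at risk at the same time since surgery, and state the control ratio.

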### **b. Objective**

1. To estimate the absolute risk of recurrent VT in patients with a history of VT who undergo various types of surgery.
2. To identify risk factors for recurrent VT in these patients.

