**b. Sample size considerations**

4731 patients were followed over time of which 700 developed a recurrence. Because we have no information on the frequency of the exposure, sample size calculations are estimations. If we assume an exposure to surgery of 10% and a 5% recurrent VT rate in the unexposed, we are able to find a relative risk of 1.6, with a power of 80%.

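### The case-control definition does not tie the recurrence to the 3-month window after surgery, so a possibly large share of the cases would not be postoperative recurrences

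*Protocol*

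**What the plan says.** The second objective (Background, b. Objective) is "To identify risk factors for recurrent VT in these patients", where the patients are those with earlier venous thrombosis who undergo surgery. Section 3a (Methods) assigns this to one analysis: "To identify high risk groups, we will perform a matched case-control study within this cohort". It gives the selection rule as "Cases are patients with a recurrent event who underwent surgery, controls are patients without a recurrent event who also underwent surgery", and the matching rule as "Cases and controls will be matched for [type of] surgery exposure". Four candidate factors are tested by logistic regression, and a prediction model follows if there are enough cases.

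Earlier in section 3a, for the cohort analysis, exposure is limited in time: "The time window of surgery exposure for each individual is defined as 3-months from the surgery date". Windows of 1 month, 6 months and 1 year are sensitivity analyses, and all other follow-up is unexposed. Follow-up runs "until the end of follow-up (end of study, dead, recurrent event or loss to follow-up, whichever occurs first".

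**The concern.** The two halves of section 3a treat the same event differently. A recurrence four years after an arthroscopy, with no later operation, falls in unexposed time in the Cox model, yet the same patient meets the case definition. The rule for cases is a complete sentence and sets no interval.

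Controls have the matching problem. They must have no recurrence at all, but need not have been observed for any period after the operation. A patient lost to follow-up two weeks after surgery qualifies as a control. A patient who recurs at month 8 was recurrence-free throughout the 3-month window, but cannot be a control and becomes a case.

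At stake is the second objective. Sex and unprovoked first event, two of the four factors, could plausibly predict recurrence at any time. With a mixed case group, an odds ratio for them does not show whether they mark patients at high risk after an operation, and a factor that acts only postoperatively is diluted. The prediction model would inherit the same cases, and the loose definition raises the count that decides whether it is built.

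**Working it through.** **The plan's own figure.** The protocol gives no figure for the case-control study. Its only calculation (section 3b) is for the cohort: 4731 patients, 10% exposed, 5% recurrence in the unexposed, relative risk 1.6, power 80%. With two-sided alpha 0.05 (assumed), 473 exposed at 8% and 4258 unexposed at 5%, the standard error of the log relative risk is √(0.92/37.85 + 0.95/212.9) = 0.170. Then 0.470/0.170 − 1.96 = 0.81, which is 79% power. The figure reproduces by this method and does not bear on the case definition.

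**Share of cases inside the window.** Inputs:
- Window: 0.25 years (section 3a).
- Postoperative hazard ratio (HR): 1.6 is the planning value in section 3b; 3 to 10 is the range the Background cites from an earlier study; 4 and 6 lie between.
- Assumed, because the protocol does not give them: one operation per patient at a uniformly distributed time, surgery before recurrence, constant baseline hazard, follow-up T of 3, 5 or 7 years. Mean time after surgery is m = T/2 = 1.5, 2.5 or 3.5 years.

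Expected recurrences are proportional to 0.25 × HR inside the window and to m − 0.25 after it, so

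share inside = 0.25 × HR / (0.25 × HR + m − 0.25).

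| HR | T = 3 | T = 5 | T = 7 | Outside window |
|---|---|---|---|---|
| 1.6 | 0.40/1.65 = 24% | 0.40/2.65 = 15% | 0.40/3.65 = 11% | 76-89% |
| 3 | 0.75/2.00 = 37.5% | 0.75/3.00 = 25% | 0.75/4.00 = 19% | 62.5-81% |
| 4 | 1.00/2.25 = 44% | 1.00/3.25 = 31% | 1.00/4.25 = 24% | 56-76% |
| 6 | 1.50/2.75 = 55% | 1.50/3.75 = 40% | 1.50/4.75 = 32% | 45-68% |
| 10 | 2.50/3.75 = 67% | 2.50/4.75 = 53% | 2.50/5.75 = 43% | 33-57% |

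A simulation calibrated so that 700/4731 = 14.8% recur by T at the baseline hazard agrees within about one percentage point at HR 1.6, 3, 6 and 10. Widening T to 2-9 years gives shares inside of 9-34% (HR 1.6), 15-49% (HR 3), 27-67% (HR 6) and 38-78% (HR 10). With two or three operations and T = 5 the shares are 21-27%, 34-41%, 51-58% and 64-71%.

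**Effect on an odds ratio (illustrations with chosen inputs).**
- Dilution: a factor carried by 30% of controls has odds ratio 2.0 for postoperative recurrence and 1.0 for other recurrence. Its prevalence in postoperative cases is 0.6/1.3 = 0.462. At a 25% share inside the window, prevalence in all cases is 0.25 × 0.462 + 0.75 × 0.30 = 0.340, and the observed odds ratio is (0.340/0.660)/(0.30/0.70) = 1.20. The same steps give 1.12 at a 15% share and 1.34 at 41%.
- Distortion: a factor carried by 50% of controls has odds ratio 1.0 postoperatively and 2.0 later. With 69% of cases late (HR 4, T = 5), prevalence in cases is 0.31 × 0.50 + 0.69 × 0.667 = 0.615, and the observed odds ratio is 0.615/0.385 = 1.60.

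**The case against.** The strongest reply is that the window is already implied. Section 3a defines surgery exposure as 3 months, places the case-control study inside the cohort, and matches on surgery exposure, using the same term. The authors may well have intended the link. But that term governs what is matched, not who is a case; its bracketed qualifier points to the kind of procedure; and no sentence applies the window to case status. Even on this reading the control rule would still lack a comparable period of observation.

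Second, a reader might infer that most cases would not be postoperative. The protocol does not establish this. It gives neither follow-up length nor number of operations, and section 3b says exposure frequency is unknown. A majority outside the window holds at HR 1.6 to 3 in every 3-month scenario run, but can fail at HR 6 to 10 with short follow-up or repeated operations.

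Third, 3 months is not an absolute boundary. The protocol says the duration of raised risk is unknown and plans windows up to 1 year. With a 1-year window, one operation and T = 5, the simulated share inside is 48% at HR 1.6 and 64% at HR 3. A recurrence after month 3 is therefore not shown to be unrelated to surgery; it is only outside the plan's primary window.

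Fourth, a literal reader might infer that surgery after the recurrence also makes a case. Cohort follow-up ends at the recurrence, so that reading is weak, and the shares above assume surgery first.

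Finally, never-recurrent controls are a recognised scheme, and the odds ratios above rest on invented inputs. Both points stand: the illustrations show that dilution and distortion can occur, not how large they will be here.

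**Conclusion.** The concern holds in this form: the case rule does not tie the recurrence to the exposure window, and the control rule requires no comparable time under observation after surgery. Followed as written, it mixes postoperative with later recurrences and does not cleanly answer the second objective.

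The share of cases affected could be large, but its size depends on the hazard ratio, follow-up and number of operations assumed in the table. The defect does not need a majority: at HR 10 with one operation and 5 years, about 47% of cases would still lie outside the window. The first objective is untouched, because its windows are explicit.

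**What to change.** Define a case as a certain recurrence within 3 months after the operation date, with 1 month, 6 months and 1 year as sensitivity analyses. Select controls who had the same type of surgery and were recurrence-free and under observation over the same interval after it. The linked procedure data described in section 2a carry the dates, so no new data are needed.

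The cost is fewer cases, wider confidence intervals and less chance of building the prediction model. If only 25% of the cases remain, with the same number of controls per case, standard errors of the log odds ratios grow by about 1/√0.25 = 2. A Cox or logistic model on all operations is an optional alternative, not a required correction.
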